### Comparators

All appointments will be made in accordance with the usual practice except for two aspects. First, the appointment letter will inform the user (for both the intervention and control arms) about the trial. The letter will explain that the investigation has been initiated by the Danish Regions and approved by the Ministry of Health and that the patient’s appointment has been randomly assigned to be subject to a fine in the case of nonattendance without notice by the patient if a letter about the fine system is attached to the appointment letter. Second, for appointments randomized to the intervention group only, a letter specifying the conditions for the fine assessment is attached to the appointment letter. This letter clearly indicates that a fine will be issued in the case of nonattendance if the patient does not give notice prior to the time of the appointment. The patients are also informed that the fine amounts to DKK 250 and that it will be issued by a central office under the local government administration (Corporate Finance, Central Denmark Region), which is open for e-mails and telephone calls during normal office hours if the patient has any questions or complaints.

The secretary registers nonattended appointments in the clinic daily. If a user shows up late, the health professionals will usually attempt to see the user anyways. A list of nonattended appointments will be automatically sent once a week to the central office administering the fine system. Similarly, this office will receive the list of included appointments once a week to handle questions and complaints. Fines will be issued once a week, and recipients are given 4 weeks before the fine is due. In the case of nonpayment, users will receive two reminders; thereafter, the collection of the fine will be handed over to the tax authority (SKAT), which will collect the fine and related expenses.

### Measures of effectiveness

The primary outcome measure is the proportion of appointments that are attended. The secondary outcomes, which are covariates, include the proportions of sociodemographics (age, sex, income, education, distance to hospital, travel time, and waiting times) and health-problem characteristics (anatomy, type of appointment and treatment costs). All parameters except for sociodemographics are automatically extracted from the electronic patient journal system into a trial registry and administratively registered in electronic trial registries. Data on sociodemographics are extracted from various, individual user-level, national registries administered by Statistics Denmark.

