**Methods/design:**

A 1:1 randomized controlled trial of scheduled outpatient appointments was used, with follow-ups until the date of appointment. The setting is an orthopedic clinic at a regional hospital in Denmark. Appointments for users who are scheduled for diagnostics, treatment, surgery, or follow-ups were included from May 2015 to November 2015. Appointments assigned to the intervention arm include an attachment of the appointment letter explaining that a fine will be issued in the case of nonattendance without prior notice. Appointments assigned to the control arm follow usual practice (same system but no letter attachment). The primary outcome is the proportion of nonattendance. Secondary outcomes are proportions of cancellations, sociodemographics, and health-problem characteristics. Furthermore, the intervention costs and production value of nonattended appointments will be measured. An analysis of effect and cost-effectiveness will be conducted based on a 5 % significance level.

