## Background

Recent hospital episode statistics from the United Kingdom show that approximately 20 % of scheduled outpatient appointments are nonattended [1]. While hospital and user cancellations each account for almost one third of the nonattended appointments, 7 % of nonattended appointments remain unaccounted for. Seven percent nonattendance is estimated to represent a cost to the healthcare system of around £790 million per year in the United Kingdom [2].

Outpatient nonattendance refers to the phenomenon of users who have an appointment but do not show up at the specified date, time, and location without giving notice. In addition to affecting the efficiency of production and thereby increasing the total costs of care, nonattendance might also delay access to care for users on waiting lists. Moreover, nonattendance has been suggested to have a detrimental effect on health outcomes [3, 4], an effect that is unevenly distributed across disease and socioeconomic groups [5, 6].

Stubbs et al. conducted a systematic literature review to assess the efficacy of various reminder interventions for reducing outpatient nonattendance such as telephone, mail, text/short message service, e-mail reminders, and open-access scheduling [7]. They found that almost all of the assessed interventions moderately reduced nonattendance. However, much of this evidence was based on observational studies, and most studies did not control for socioeconomic status and other relevant factors such as age, sex, waiting time, and health-problem characteristics. The recognition of a need for further high-quality studies has been confirmed by similar systematic reviews [8–10].

Another means for reducing outpatient nonattendance, for which there appears to be only vague empirical evidence, is to penalize nonattendance by a fine. According to neoclassical economic theory, user behavior can be influenced by financial incentives. The introduction of a fine for nonattendance will create a stronger incentive for users to appear at their scheduled appointments [11]. This has been demonstrated in two earlier observational studies where the introduction of fines led to a 14 % reduction and a 54 % reduction in nonattendance [12, 13]. These studies, however, only represent before-and-after scenarios, do not consider the likely influence of exogenous factors, and have limited sample sizes. Furthermore, the external validity is questionable due to the 20-year time lag.

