In Denmark, the introduction of fines for nonattendance in hospital outpatient clinics has been debated for years [14]. In 2005, a collaborative agreement between the Danish Regions and the Danish Medical Association opened the opportunity for privately practicing specialists to issue nonattendance fines of Danish kroner (DKK) 250 for consultations and DKK 500 for surgical procedures (1 EUR = 7.45 DKK) [15]. Overall, the expected benefits were related to a better use of resources, whereas concerns were expressed about the detrimental effect on equal access for equal needs, as the fines would impact the most vulnerable users most strongly. Moreover, the use of fines was seen as a break with the fundamental value of free and equal access to healthcare and a potential threat to the patient-health professional relationship, which ideally should be independent of financial interests [14].

Although 10 years have passed since the regulatory context cleared the way for fines in the Danish healthcare system for privately practicing specialists, no systematic evidence on the resulting practice, efficacy, or effect appears to have been reported. Therefore, the Danish Regions have decided that the effect of using fines to moderate nonattendance at somatic, hospital-based, outpatient clinics in Denmark should be scientifically investigated [16]. This trial is a result of that decision and, in accordance, the aim of this trial is to investigate the effect of fines on nonattendance in a hospital-based outpatient clinic. The primary hypothesis is that the risk of fines will incentivize healthcare-service users to attend appointments more often than if no risk of fines is associated with nonattendance of a planned appointment. A secondary hypothesis is that the pattern of attendance will be affected by the risk of fines in terms of who attends (user characteristics) and what type of appointment is being attended (appointment characteristics). The rationale for the second hypothesis is to address the political focus on preserving equal access to healthcare and on variation in provider efficiency. Finally, a third hypothesis is that the use of fines in routine practice will be cost effective.

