### Setting

The Department of Orthopedic Surgery at Viborg Regional Hospital consists of an outpatient clinic and a ward. The outpatient clinic has 18,500 scheduled appointments a year, of which approximately 19 % are cancelled and 5 % are nonattended (see Table 1). Medical secretaries manage the booking via an electronic booking system that automatically generates appointment letters that are sent to users. Apart from this system, a substantial number of appointments are scheduled without a sufficient time lag to allow for the dispersal of appointment letters (e.g., in cases of acute health problems) and thus are not considered in the present study.

**Table 1 Tab1:** Historical number of cancelled (% of scheduled) and nonattended (% of noncancelled) appointments from April 2014 to March 2015 for the study setting

		Cancelled appointments			
	Scheduled appointments	By hospital	By user	Total	Nonattended appointments
April 2014	1,473	187 (13)	95 (6)	282 (19)	55 (5)
May 2014	1,467	223 (15)	105 (7)	328 (22)	64 (6)
June 2014	1,869	307 (16)	94 (5)	401 (21)	83 (6)
July 2014	1,082	175 (16)	66 (6)	241 (22)	50 (6)
August 2014	1,562	262 (17)	52 (3)	314 (20)	68 (5)
September 2014	1,661	270 (16)	151 (9)	421 (25)	62 (5)
October 2014	1,634	208 (13)	223 (14)	431 (26)	41 (3)
November 2014	1,744	205 (12)	89 (5)	294 (17)	71 (5)
December 2014	1,583	190 (12)	52 (3)	242 (15)	62 (5)
January 2015	1,511	166 (11)	30 (2)	196 (13)	60 (5)
February 2015	1,387	118 (9)	36 (3)	154 (11)	48 (4)
March 2015	1,520	147 (10)	44 (3)	191 (13)	50 (4)
Total	18,493	2,458 (13)	1,037 (6)	3,495 (19)	714 (5)

Note: All appointments booked by appointment letter are included (not appointments booked by telephone)

Users can call or e-mail to give notice of nonattendance or to have their appointment rescheduled. The secretary is open for telephone calls between 0745 and 1430 on weekdays and can be contacted via e-mail 24 hours a day/7 days a week. A short message service (SMS) reminder system is used to prevent nonattendance; however, this can only be used for follow-up appointments, as the user’s phone number is not available until an initial visit has been attended or if the user has attended the clinic before. Based on historical data, we expect that 20–30 % of scheduled users will continue receiving SMS reminders.

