### Analysis of effectiveness

The principle of intention-to-treat will be used for analysis, and each of the outcome parameters will be compared between the intervention and the control groups. A simple test of proportions will be used to test the primary hypothesis. The secondary hypotheses will be tested in two probit regressions: one for user characteristics and one for appointment type characteristics. Both models will have attendance as the dependent variable and a randomization group dummy and user/appointment type characteristics as covariates along with interaction terms for the randomization group dummy and the covariates. The interpretation of the interaction terms will then be the effect modification of the covariates, which is the same as a differentiated effect of fines on different users/types of appointments. A significance level of 0.05 will be used for all analyses.

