### Analysis of cost-effectiveness and budget impact

The primary outcome measure will be adopted from the effectiveness analysis (proportion of nonattendance), and the cost parameter will include the net cost of the intervention on the consequences to productivity. The incremental cost effectiveness ratio for the healthcare sector will be analyzed to illustrate the impact of the fines on technical efficiency [20]. The main result will thus be the extra cost of preventing an extra user from not attending, which will be reported as a mean value with 95 % confidence intervals, given that both nominator and denominator are positive; otherwise, the net benefit framework will be adopted to accommodate negative components of the ratio [21, 22]. A sensitivity analysis will be conducted to assess the robustness of the results with respect to methodological choices. The cost-effectiveness analysis will be supplemented with a simple budget impact analysis that considers the revenue from fines less the collection costs [23].

Missing data is not relevant when using register-based data.

The data will be handled in accordance with the Data Protection Act, and the establishment of a research register was approved by the Legal Office at the Central Denmark Region (journal no. 1-16-02-288-15), which has been delegated the authority to handle local research projects by the national Data Protection Agency. Only the researchers authoring this protocol will have access to the data.

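### The primary outcome is attendance in one section and nonattendance in others, and with no denominator fixed the two need not give the same result

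*Protocol article*

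**What the plan says.** The protocol article names the primary outcome in two ways.

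- **Attendance.** Measures of effectiveness: "The primary outcome measure is the proportion of appointments that are attended". The primary hypothesis in Background matches it: "the risk of fines will incentivize healthcare-service users to attend appointments more often". For the probit models, Analysis of effectiveness says: "Both models will have attendance as the dependent variable".
- **Nonattendance.** Abstract (Methods/design): "The primary outcome is the proportion of nonattendance". The cost-effectiveness section claims to take its outcome over from the effectiveness analysis, yet names the other one: "The primary outcome measure will be adopted from the effectiveness analysis (proportion of nonattendance"). Sample size is built on a nonattendance rate falling from 4.8 % to 3.22 %.

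Background defines nonattendance as users who "do not show up at the specified date, time, and location without giving notice", so a cancelled appointment is neither attended nor nonattended. The Abstract treats cancellation as a result of its own: "Secondary outcomes are proportions of cancellations, sociodemographics, and health-problem characteristics".

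The denominator is not fixed. The Setting text puts both rates on scheduled appointments: "of which approximately 19 % are cancelled and 5 % are nonattended (see Table 1"). The caption of Table 1 gives cancellations as a share of scheduled appointments but nonattendance as a share of noncancelled ones. Measures of effectiveness speaks of appointments without restriction, and Analysis of effectiveness adopts intention-to-treat.

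**The concern.** Under Comparators, the fine falls only on a user who stays away without prior notice. Cancelling therefore avoids it as fully as attending does, and a direct response to the letter is to move from nonattended to cancelled. That lowers nonattendance and leaves the share of all appointments attended unchanged.

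The section that defines the outcomes would then have the primary test run on a quantity that may barely move, while the power statement refers to another. An analyst could follow either section and be faithful to the document. Analysis of effectiveness also does not say whether a cancellation counts as a zero in the probit models or is left out.

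**Working it through.** **Inputs.** Table 1 totals: 18,493 scheduled; 3,495 cancelled (1,037 by users, 2,458 by the hospital); 714 nonattended. Sample size: 4.8 % to 3.22 %, 3,250 per arm, 90 % power. Alpha is 0.05, assumed two-sided because that reproduces the stated size.

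**Formula.** Power = Φ((|p1 − p2| − 1.96·s0)/s1), with s0 = √(2p̄(1 − p̄)/n), s1 = √((p1(1 − p1) + p2(1 − p2))/n) and p̄ the mean of p1 and p2.

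**1. The plan's own figure.** For 4.8 % against 3.22 % at n = 3,250: s0 ≈ s1 ≈ 0.00487, so (0.0158 − 0.00954)/0.00486 = 1.29 and power is 0.901. The required size is 3,239 per arm. The stated 3,250 reproduces.

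**2. The possible results in Table 1.** Attended = 18,493 − 3,495 − 714 = 14,284.

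| Result | Of 18,493 scheduled | Of 14,998 noncancelled |
|---|---|---|
| Attended | 77.2 % | 95.2 % |
| Nonattended | 3.86 % | 4.76 % |
| Cancelled | 18.9 % (5.6 % user, 13.3 % hospital) | – |

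Over scheduled appointments, attended plus nonattended is 81.1 %. Over noncancelled appointments it is 100 %. The 4.8 % planning rate matches the noncancelled column.

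**3. The planned effect on the scheduled basis.** The relative reduction is 1.58/4.8 = 0.329. In points of scheduled appointments it is 1.58 × 0.811 = 1.28 (3.86 × 0.329 gives 1.27; the gap is the rounding of 4.76 to 4.8).

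**4. Power at 3,250 randomised per arm.**

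| Outcome and basis | Comparison | Power |
|---|---|---|
| Nonattended, noncancelled | 4.8 % v 3.22 % | 0.90 |
| Attended, noncancelled | 95.2 % v 96.78 % | 0.90 (same variance, same difference) |
| Nonattended, scheduled | 3.86 % v 2.59 % | (0.0127 − 0.00859)/0.00438 = 0.94, so 0.83 |
| Attended, scheduled, every avoided no-show attends | 77.24 % v 78.52 % | (0.0128 − 0.0202)/0.0103 = −0.72, so 0.24 |
| Attended, scheduled, half attend | 77.24 % v 77.88 % | (0.0064 − 0.0203)/0.0103 = −1.34, so 0.09 |
| Attended, scheduled, all cancel | no difference | no effect to detect |

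**5. Illustrative counts.** Assume 19 % cancelled and 3.86 % nonattended of 3,250 per arm. Control is then 2,507 attended, 125 nonattended and 618 cancelled. Reduce nonattended to 84 in the intervention arm: p = 0.004 over all appointments, wherever the 41 avoided no-shows go. For attendance over all appointments, p = 1.00 if all cancel (2,507), 0.55 if about half attend (2,527) and 0.22 if all attend (2,548).

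**The case against.** The strongest reply is that the two outcomes are the same. Table 1 reports nonattendance among noncancelled appointments and the 4.8 % planning rate sits on that basis, where attended is exactly one minus nonattended and the test and power are identical. The arithmetic stands. It does not settle the matter, because no section adopts that denominator for the primary outcome. It also drops appointments by an event after randomisation that the fine can change, which fits poorly with intention-to-treat.

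A second reply is that the intended outcome is recoverable: the aim, the Abstract, the definition, the power calculation and the cost-effectiveness section all point to nonattendance. This is largely right and shows which way to reconcile. Researcher blinding through the analysis, as stated under Randomization and consent, limits selection by result but does not remove the need to fix the outcome.

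Three stronger readings are tempting but not supported.

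- A reader might infer that one dataset could give opposite answers. The scenarios give significant against not significant, never significance in both directions. With 4.8 % of all appointments nonattended, all avoided no-shows cancelling and 2 further points of cancellation, attendance falls with p = 0.06.
- A reader might infer that the 90 % power belongs to nonattendance alone. It belongs to the noncancelled denominator: attendance has it there too, and nonattendance has about 83 % over all appointments.
- Applying the 1.58-point change to 77.2 % gives 34 % power, but this mixes the two bases. The consistent figure is about 24 %.

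Nor is all of the 19 % open to change by the fine: about 13 points are hospital cancellations, which a fine on users would not be expected to move.

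**Conclusion.** The concern holds in limited form. The current text contradicts itself on the primary outcome and leaves the denominator open. The contradiction has consequences only if cancelled appointments stay in the denominator, which is the plain reading of Measures of effectiveness combined with intention-to-treat. On that reading a real one-third fall in nonattendance is detected with about 83 % power as nonattendance, but with at most about 24 % as attendance. The sample size is correct for the basis on which it was calculated.

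These figures assume that the trial's cancellation and nonattendance rates resemble Table 1, that the split of avoided no-shows between attending and cancelling is as shown (the document gives none), and that 3,250 per arm counts all randomised appointments. If 3,250 instead counts noncancelled ones, about 3,250/0.81 = 4,012 per arm are randomised. The same formula then gives about 90 % for nonattendance and about 28 % for attendance over all appointments, so the contrast remains.

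**What to change.** - **Outcome.** Name nonattendance without prior notice at the randomised index appointment as the single primary outcome. Align the primary hypothesis in Background, Measures of effectiveness and Analysis of effectiveness with the Abstract, Sample size and cost-effectiveness sections.
- **Denominator.** State it as all randomised index appointments under intention-to-treat, with the noncancelled basis as a sensitivity analysis.
- **Power.** Restate the planning rate and power on that basis: 3.86 % from Table 1, and about 83 % for the same one-third relative reduction. Say whether the 6,500 counts appointments before or after cancellation.
- **Reporting.** Tabulate attended, nonattended, cancelled by user and cancelled by hospital by arm. Cancellations are already a secondary outcome in the Abstract and Sample size; the split is the addition.
- **Probit models.** State how cancellations are coded. Use nonattendance as the dependent variable to match the primary outcome, and keep attendance as a secondary model, because the secondary hypothesis in Background concerns who attends.
- **Timing.** Trial status says the trial closed on 1 December 2015, so date the clarification relative to data access.

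The cost is a less favourable stated power and one extra set of models. No new data are needed.

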### Measures of costs

The opportunity costs are considered from a Danish healthcare perspective and include the intervention cost as well as the productivity costs related to nonattendance. Microcosting of the intervention will be used to estimate the costs of a routine-based system that manages the issuing of fines, questions, complaints, reminders, and the handover of claims to the tax authorities in the case of nonpayment after reminders. The cost determination will be based on detailed time registrations made by the central office undertaking the administration of fines. Time registrations will be integrated in the administrative system at the appointment level and will be valued using average gross staff salaries. The cost of utensils will be added to the standard overhead rate for the administration.

The cost determination of productivity loss due to nonattendance will be estimated by the production value of nonattended appointments if they had been attended. As a worst-case estimate, implying no flexibility of production, the full tariffs of the Diagnosis-Related-Grouping system will be used to value productivity loss. As a best-case estimate, implying that the production is almost fully flexible and will simply take the next user in the case of nonattendance, only a proportion of the production value will be used. The relevant levels of the worst-case and best-case scenarios will be informed from qualitative and observational studies that are conducted in another test department, which is fully exposed to the fine protocol at the departmental level.

It should be noted that revenue from fines is a transfer of money between taxpayers who do not attend scheduled appointments and all other taxpayers (and is not an economic opportunity cost). However, the revenue net of the costs for administrating the fine system is considered for budget impact analysis.

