### Sample size

Based on department statistics, a nonattendance rate of 4.8 % and a volume of 6,500 eligible appointments during a time window of 7 months are assumed. This time window was adopted to balance of arguments concerning effect size and stability in the study, which are exerted for restructuring and cost cutting after the 7 months. A minimum reduction of 1.58 % (from 4.8 % to 3.22 %) was found using a chi-squared test and a 90 % power level. The randomization ratio is 1:1, which indicates that 3,250 users are required in each arm. The power to detect similar impacts on the secondary outcome parameters of cancellations will be higher due to higher baseline proportions. The power to detect the impact on sociodemographics will depend on the scaling and the relevant level of relative risk reduction [19].

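### Productivity loss is valued only on nonattended slots, so a no-show that becomes a late, unfilled cancellation is credited as a saving in the cost-effectiveness result

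*Protocol article*

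**What the plan says.** Four statements in the protocol article bear on the point.

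- **When the fine applies (Comparators).** The attached letter says a fine follows nonattendance "if the patient does not give notice prior to the time of the appointment". No minimum notice period is set. Under Setting, notice can be given by telephone in weekday hours or by e-mail at any time. The Background defines nonattendance in the same way, as absence without notice.
- **What is valued as lost (Measures of costs).** Productivity loss "will be estimated by the production value of nonattended appointments if they had been attended". The worst case uses full Diagnosis-Related-Grouping tariffs and supposes that production has no flexibility. The best case supposes almost full flexibility and uses only a proportion of the production value.
- **The effect measure and main result (Analysis of cost-effectiveness and budget impact).** The effect is the proportion of nonattendance. "The main result will thus be the extra cost of preventing an extra user from not attending".
- **Cancellations.** They are a secondary outcome in the Abstract and are mentioned under Sample size. Nowhere is a cancelled slot given a cost, and late cancellations are not separated from early ones.

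**The concern.** The fine rewards notice, however late. Only the intervention arm receives the fine letter, so the incentive to turn a silent no-show into a last-minute message exists mainly in that arm. If the slot cannot be refilled, the clinic loses as much as it would from a no-show. The planned valuation nevertheless records no loss, because the appointment is no longer coded as nonattended.

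The two cost scenarios do not repair this. They change the value attached to each nonattended slot, not which slots count as lost. The worst case is the clearest instance: it assumes that an empty slot cannot be put to other use, yet it treats a slot cancelled minutes beforehand as though it had been used.

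At stake is the third hypothesis, that fines are cost effective in routine practice. The cost-effectiveness ratio is meant to illustrate technical efficiency and to inform national policy. Fewer no-shows without more used slots would not be an efficiency gain.

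**Working it through.** **Inputs from the protocol article.** Sample size assumes "a nonattendance rate of 4.8 % and a volume of 6,500 eligible appointments", a fall to 3.22 % (1.58 percentage points) and 3,250 users per arm; the reduction "was found using a chi-squared test and a 90 % power level". Analysis of effectiveness gives the level: "A significance level of 0.05 will be used for all analyses". Sidedness is not stated.

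**The plan's own figure.** For two proportions with pooled variance under the null, two-sided and without continuity correction:

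n = [1.960 √(2 × 0.0401 × 0.9599) + 1.2816 √(0.048 × 0.952 + 0.0322 × 0.9678)]² / 0.0158² = 3,239 per arm.

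This agrees with 3,250, at which power is 90.1 %. The planned effect is therefore a sound basis for an illustration.

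**No-shows credited as avoided at the planned effect.** Control: 3,250 × 0.048 = 156.0. Fine arm: 3,250 × 0.0322 = 104.65. Difference: 51.35 slots.

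**Assumed quantities.** Let f be the share of avoided no-shows that become late cancellations. Let r be the share of those slots refilled because notice was given, beyond whatever the scenario's unit value already allows for a no-show. The documents give neither.

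- Credited gain = 51.35 × V, where V is the per-slot value in the scenario.
- Gain in used slots = 51.35 × [1 - f(1 - r)] × V.
- Overstatement factor = 1 / [1 - f(1 - r)].

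Slots saved, with the factor in brackets:

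| f | r = 0 | r = 0.5 | r = 1 |
|---|---|---|---|
| 0 | 51.35 (1.00) | 51.35 (1.00) | 51.35 (1.00) |
| 0.25 | 38.51 (1.33) | 44.93 (1.14) | 51.35 (1.00) |
| 0.50 | 25.68 (2.00) | 38.51 (1.33) | 51.35 (1.00) |
| 0.75 | 12.84 (4.00) | 32.09 (1.60) | 51.35 (1.00) |
| 1 | 0 (unbounded) | 25.68 (2.00) | 51.35 (1.00) |

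**What the factor depends on.** V and the 51.35 cancel, so the factor depends on neither the tariff nor the effect size. For any f above 0 and r below 1 it exceeds 1, so the direction is fixed. It applies to the productivity component, not to the whole ratio. With intervention cost C, the planned net cost is C - 51.35V; on used slots it is C - 51.35V[1 - f(1 - r)].

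**The worst case.** If production has no flexibility, a late-cancelled slot is not refilled, so r = 0 and the factor is 1/(1 - f). Giving such a slot no loss amounts to setting r = 1, the opposite of the scenario's premise.

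**The case against.** **The size is not evidenced.** This stands. The table is an identity with assumed inputs. A reader might infer that the gain is overstated 1.3, 2 or 4 times; the documents support none of these values, and the bias is nil if late-cancelled slots are refilled. The count of 51 is also soft. In Table 1 nonattendance is a percentage of noncancelled appointments: 714 / (18,493 - 3,495) = 4.8 %. If the 3,250 per arm include cancellations at the historical 19 %, the count is 3,250 × 0.81 × 0.0158 = 42. The factors do not change.

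**A full saving is credited only in the worst case.** This stands too. The best case credits a proportion of production value. That proportion rescales every no-show alike, however, and still gives a late cancellation no loss.

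**The effectiveness estimate is not biased.** A reader might infer that it is. The documents define nonattendance as absence without notice and tie the fine to it, so prompting notice is part of the intended response.

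**Other safeguards exist.** Cancellations are to be compared by arm, so a shift could be seen beside the cost result. That comparison does not separate late from early cancellations and does not enter the costs. The Discussion concedes that provider-level productivity cannot be evaluated here and points to a parallel study, but a productivity saving is still computed. The planned sensitivity analysis on methodological choices is generic. A fuller plan might name this scenario; the point here is that the valuation rule the article does fix goes the wrong way for these slots.

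**Clinic secretaries' time.** Intervention cost is limited to the central office: "The cost determination will be based on detailed time registrations made by the central office undertaking the administration of fines". A reader might infer that handling extra cancellations would add a material cost. No figure is given and the net direction is unclear, since secretaries also spend time registering no-shows. It adds no weight.

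**Conclusion.** The point holds for the productivity component of the cost-effectiveness analysis. A no-show that becomes a late, unfilled cancellation is assigned no loss and credited with the whole per-slot value of the scenario. In the worst case this contradicts the scenario's own premise. Where it occurs, the error can only favour fines.

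The size cannot be determined from the documents. It runs from nothing (f = 0 or r = 1) to the whole productivity gain (f = 1 and r = 0). This rests on the conversion happening in the fine arm, which the incentive makes plausible but which the documents do not show.

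The primary effectiveness test is not affected. It would go too far to say that the trial's cost-effectiveness conclusion will be wrong. What can be said is that the planned valuation cannot distinguish a real gain in used capacity from a relabelling of empty slots. This is a worthwhile, inexpensive improvement to a secondary economic result.

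**What to change.** Add a named sensitivity analysis to Measures of costs and to Analysis of cost-effectiveness and budget impact, in one of two forms.

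- **If the booking extract holds cancellation times:** state a refill window in advance and vary it. Value user cancellations inside the window at the same production value as nonattended slots. Use unused slots (nonattended plus late-cancelled) by arm as the effect measure.
- **If it does not:** value the fine arm's excess of user cancellations over control at that production value, as a bound. This treats every extra cancellation as a lost slot, and it assumes that the fine does not reduce cancellations that would have been made anyway.

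Recruitment has closed, but the change is analytic only. The first form needs one further field from data that are already extracted electronically (its availability is an assumption); the second needs only the cancellation counts by arm. The price is that a refill window must be chosen and varied, and that the result may become less favourable to fines.
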